### Qualitative analysis

In addition to the quantitative data on potential determinants of intervention effectiveness, qualitative data could help to reveal factors that may explain baseline and intervention effect differences between preschools. Specifically, we will compare preschools where the intervention is particularly successful and those at which the intervention appeared to fail and will report this using a contrasting case studies approach. Furthermore, only preschools where the intervention was implemented to an acceptable degree (at least one project realized) will be included into the analysis per protocol to grasp the "true" effect of the intervention.

Our qualitative data also serves to explore the acceptance of interventions and to monitor adoption, implementation and maintenance of the parent-focused intervention. Specifically, we will use template analysis to validate previously under-recognized themes we perceive might be related to barriers and resources to the adoption and implementation of the intervention by successive readings and persistent immersion in transcribed text from interviews with head teachers and in documentation generated by the PA teacher [66]. The validity of themes that emerge from this analysis will be tested through an iterative process of review by two independent reviewers who seek refuting or confirmatory evidence in subsequent interview texts.

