### Intervention structure

As part of the agenda at a regular convocation of parents and teachers, we introduced our intervention using a descriptive video. Following this, parents and teachers were encouraged to discuss barriers and resources for PA within their preschool and generate further ideas on how to enhance the physical activity of their families and among children in their local preschool. Subsequent steps over the course of three follow-up parent-teacher meetings consisted of 1) holding a workshop for project selection and establishing small project-specific teams, 2) team presentations to all parents as a way to motivate a greater number of parents, and 3) a workshop for planning the implementation. Interested parents and teachers were encouraged to identify up to four project ideas that could be taken either from the menu of project ideas or designed *de novo*. We encouraged new ideas, especially if they promoted PA connected to the childrens' everyday life, if they were inexpensive and relatively simple to implement and sustain. To help parents further, we made specially trained physical activity teachers available to offer support by helping to coordinate parent activities (e.g., by proposing time-lines), encourage participation and document the implementation of the project(s).

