**Figure 2 F2:**
[figure not shown]
**Evaluation design accounting for seasonal differences and using a waiting list control**. CONT = gym lessons (existing state-sponsored programme). INT = participatory parent-focused intervention plus simultaneous gym lessons. X1 and X2: randomization time points, X1 = autumn, X2 = spring. ---- children enrolled and measured, but no intervention/gym lessons.

Preschool assignment was blinded through the use of sequentially numbered, sealed envelopes. Preschools in the control arm (CONT) (n = 20; 371 children) receive the state-sponsored programme's gym lessons over six months as the sole intervention. Parents of children enrolled at preschools in the intervention arm (INT) (n = 17; 370 children) receive the participatory intervention, while their children also participate in the gym lessons. The participatory parent-focused intervention runs simultaneously with the gym lessons over the first six months, but continues for a total of at least nine months.

To account for seasonal differences in physical activity [34,35], the study was implemented at two time-points during the year: half of the preschools started the intervention in autumn 2008 with the other half starting in the spring 2009. To account for changes that occur as a consequence of physical maturation in children over time, the participatory intervention arm served as waiting list control during the first six months. Due to the participatory nature of the intervention, it was not possible to blind study participants or intervention providers. However, those involved in outcome assessment will be blinded to intervention assignment.

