### Process measures

We carefully examine the extent to which the intervention is adopted and implemented and whether features of the context in which the intervention is delivered mediate or moderate intervention outcomes. Mediating factors were defined as contextual factors predisposing for or enabling the intended behavioural change, which might lie on the causal pathway from intervention to outcome. Moderating factors were qualitative or quantitative variables that might affect the direction or strength of the relation between intervention and outcome [60]. General Systems theory, for example, suggests the degree of teacher or parent commitment, the co-existence of other preschool programmes and the preschool physical environment as moderating factors. We therefore conduct a thorough process evaluation, which consists of face-to-face, semi-structured key informant interviews with the head teacher at each site and each measurement point. Interviews have been recorded and are currently being transcribed. These data serve as the basis for qualitative analyses to identify emerging issues related to intervention implementation.

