### Assessment of intervention effectiveness

The intervention effectiveness is assessed by an intention-to-treat analysis.

Descriptive statistical analysis will be performed on all outcome measures. If needed, data will be transformed to better meet the assumptions of standard inferential statistical tests. We will use multilevel models to account for the structure of our data and for missing data on any of the measurements. In the multilevel model, repeated measurement of outcomes for each child will be considered the first "level"; these data are nested within preschools, which represent the second level. Differences between intervention and control group in primary and secondary outcomes will be analyzed in terms of fixed effects in the multilevel regression model, with age, sex, SES, immigration status and baseline BMI/accelerometer counts included as covariates on the individual level. In secondary analyses, the effect moderation by the preschool context as rated by qualitative data, as well as the level of implementation and adoption of the intervention will be analyzed.

Previous work documents a higher prevalence of overweight [63] and lower levels of physical activity [64] among immigrants. Because of the potential public health implications, we will conduct subgroup analyses at the child level comparing outcomes for normal-weight versus overweight children and for immigrant versus non-immigrant children. Subgroup analyses at the preschool level will be performed for rural versus non-rural locations and intervention timing (autumn versus spring) to assess the presence of potential effect modifiers.

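### The per-protocol rule can be applied only to the intervention arm, so its result is a selected, non-randomised comparison and cannot be presented as the 'true' effect

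*Protocol article*

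**What the plan says.** The main analysis is clear. Under Assessment of intervention effectiveness: "The intervention effectiveness is assessed by an intention-to-treat analysis".

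A second analysis appears under Qualitative analysis: "only preschools where the intervention was implemented to an acceptable degree (at least one project realized) will be included into the analysis per protocol". Its stated purpose is "to grasp the 'true' effect of the intervention".

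On the two arms, Recruitment and randomization says: "Preschools in the control arm (CONT) (n = 20; 371 children) receive the state-sponsored programme's gym lessons over six months as the sole intervention". For the other arm: "Parents of children enrolled at preschools in the intervention arm (INT) (n = 17; 370 children) receive the participatory intervention".

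On how projects arise, Intervention structure says: "Interested parents and teachers were encouraged to identify up to four project ideas".

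Among the secondary analyses, the effectiveness section lists effect moderation by preschool context, and continues: "as well as the level of implementation and adoption of the intervention will be analyzed".

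**The concern.** Realising a project happens after randomisation and is possible in one arm only. A rule that filters on it breaks the balance that randomisation gave, unless the preschools that realise a project would have had the same outcomes anyway as those that do not.

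The protocol gives reasons to doubt that. Projects come from parents and teachers who are interested. Covariates/confounders says that data are collected on characteristics that could influence both uptake of the intervention and its success. Process measures adds that General Systems theory "suggests the degree of teacher or parent commitment, the co-existence of other preschool programmes and the preschool physical environment as moderating factors".

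The same difficulty affects implementation level as a moderator. The score is built from project and meeting records that exist only where the intervention was delivered. Controls have no value, so an interaction between arm and implementation cannot be estimated.

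What is at stake is the claim attached to the supplementary result: a selected comparison reported as the 'true' effect could be read as stronger evidence than the randomised one.

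**Working it through.** **Applying the rule to each arm.** None of the 20 control preschools can meet the criterion. Literally applied, the rule leaves 0 controls and no comparison. The only workable reading keeps all 20 controls and a subset of the 17 intervention preschools. The text does not say this; it is inferred.

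**What the model adjusts for.** The effectiveness section lists age, sex, SES, immigration status and baseline BMI or counts, all at the individual level. The Abstract also mentions preschool-level covariates, but the analysis section names none. Commitment and context are not in the list.

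**Inputs for an illustration** (Sample size and power considerations): SD 38.1 counts/15 s, ICC 0.1, target 0.5 SD = 19.05, power 0.9, two-sided alpha 0.05.

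**The plan's own figure first.** Per arm without clustering: 2 × ((1.960 + 1.282)/0.5)² = 84.06. Cluster size 504/24 = 21, so the design effect is 1 + 20 × 0.1 = 3. Total 2 × 84.06 × 3 = 504.4, against 504 stated; 504/0.9 = 560, as stated. The sample size is not at fault.

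**Size of a selection effect with no true effect.** Between-preschool SD = 38.1 × √0.1 = 12.05. Let p be the share of intervention preschools that implement, and ρ the correlation between the propensity to implement and the preschool's outcome level. Then

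spurious difference = ρ × 12.05 × φ(z)/p,

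where z is the normal quantile cutting off a share p. The protocol gives neither p nor ρ; both are assumptions. For p = 12/17, φ(z)/p = 0.488, so ρ = 0.3 gives 0.3 × 12.05 × 0.488 = 1.8 and ρ = 0.8 gives 4.7.

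| Share implementing | ρ = 0.3 | ρ = 0.8 | % of 19.05 |
|---|---|---|---|
| 0.9 | 0.7 | 1.9 | 4–10 |
| 0.8 | 1.3 | 3.4 | 7–18 |
| 12/17 | 1.8 | 4.7 | 9–25 |
| 0.5 | 2.9 | 7.7 | 15–40 |

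With ρ = 0 the difference is zero.

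**False positives.** Simulated t-tests on preschool means (17 against 20 preschools before exclusion, 5,000 runs, no true effect, no baseline adjustment) gave these rates in favour of the intervention, against a nominal 2.5%:
- 20% excluded: 2.5% at ρ = 0 and 5.3% at ρ = 0.5
- 30% excluded: 7.4% at ρ = 0.5 and 13.8% at ρ = 0.8
- 50% excluded: 12.3% at ρ = 0.5

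**Effect of baseline adjustment.** If adjustment has slope b, about (1 − b) of a stable level difference remains. Assuming b = 0.5, the range 1.8–4.7 becomes 0.9–2.4 (5–12% of 19.05). In a pure change comparison, a stable level cancels. What then remains is a difference in trend between committed and other preschools, which cannot be sized from the document.

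**Complier-average alternative.** Let e₁ be the effect in preschools with a project and e₀ the effect in those without. Intention-to-treat estimates p·e₁ + (1 − p)·e₀. Dividing by p gives e₁ + ((1 − p)/p)·e₀. With p = 12/17 the excess is (5/12)·e₀ = 0.42·e₀, which is zero only if preschools without a project gain nothing.

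**The case against.** The strongest reply is that this is a supplementary analysis. Effectiveness is assessed by intention-to-treat, no text gives the per-protocol result priority, and the article itself puts the word true in quotation marks. That stands, and it limits the point. A reader might infer that the trial's effectiveness conclusion is biased, or that the per-protocol result would be preferred after a null intention-to-treat result. The document supports neither.

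Second, one might extend the moderation objection to adoption. That fails: Indicators of intervention adoption and implementation says that adoption is assessed before the intervention starts and rated over all preschools. Context is also rated for each preschool. The objection reaches implementation level only. Even there the sentence is ambiguous, since it could mean that implementation is analysed in its own right.

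Third, the support for a common cause is indirect. Process measures calls commitment and environment moderators of the effect; it does not say that they decide whether a project is realised. Covariates/confounders is better support, although the confounders it names are child-level and are largely in the model. What remains unadjusted is preschool-level interest and commitment, on which realising a project plausibly depends.

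Fourth, the illustrated figures ignore the planned baseline adjustment and rest on assumed values. This is correct, and they should not be quoted as the expected bias.

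**Conclusion.** The point holds as a moderate one. The rule as written is either unusable (no controls) or yields a comparison of intervention preschools selected after randomisation with unselected controls. Such a comparison cannot carry the label of a 'true' effect. Intention-to-treat is untouched.

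Bias towards benefit is the probable direction, because interested communities are more likely both to implement and to have active children. It is not certain: the sign follows from an assumed positive correlation. The illustration of 1.8 to 4.7 counts/15 s assumes 12 of 17 preschools implementing, correlations of 0.3 to 0.8 and no baseline adjustment; with adjustment it would be smaller. The conclusion does not depend on that range. It depends on the filter acting after randomisation, in one arm, on something related to local interest.

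**What to change.** - Base effectiveness conclusions on intention-to-treat alone.
- Move the per-protocol rule to the effectiveness section. State how control preschools are handled, label the analysis exploratory and non-randomised, and remove the claim to a 'true' effect.
- Analyse implementation level descriptively within the intervention arm, not as a moderator of the arm effect. Keep as moderators only adoption and preschool context rated before the start in all preschools. Because head-teacher interviews take place at every measurement point, specify that the context rating uses the baseline one.
- If an effect of implementation is wanted, add a preschool-level complier-average estimate as a sensitivity analysis, with random arm as the instrument for at least one project realised. State that it assumes no effect in preschools without a project. State also that the video, meetings, workshops and idea materials offered to them (Intervention components, Intervention structure) make this doubtful, and that the estimate is too large if they benefit.

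The cost is a short change to the analysis text, with no new data. The optional estimate has a wider interval than intention-to-treat and an assumption that must be defended.

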### Ethics and human subjects' confidentiality

All parents of children participating in the gym lessons received written information on the study and further oral explanation by preschool teachers, if needed. The parents of all children participating in the study provided their informed consent. Ethical approval was granted by the Ethics committee of the Medical Faculty Mannheim, Heidelberg University (ID 2008-275N-MA).

## Discussion

In the present paper we describe the design and evaluation of a public health intervention specifically aiming at promoting preschoolers' PA by involving the individual child's and peers' parents. The study design employing mixed methods to assess the intervention efficacy and implementation within a cluster-randomized controlled trial may serve as a framework for evaluating future public health interventions in preschool settings.

The intervention we describe here has several unique elements. First, we draw from General Systems theory as a conceptual framework for the design of our intervention. This theory suggests, for example, that participation of the whole preschool social network (parents, children, grandparents and teachers) may allow for a more customized approach, which in turn may increase the acceptance and effectiveness of the intervention. This theory also suggests that the social network developing among participants of a participatory intervention may lead to longer-term sustainability. To enable network building among participants, we use readily available website authoring technology to create a shared information platform. This feature also has the potential to sustain effects of the intervention following the end of the formal study intervention by providing a no-cost resource to a broad community of parents and teachers with common interests. Second, our intervention moves beyond a knowledge-based or educational approach by fostering "learning by doing" within child and parent peer groups. Third, we have designed and implemented a multi-component intervention that incorporates an existing state-sponsored programme to promote PA. As a fourth element we use a multi-pronged strategy to change behaviours. In many interventions, for example, the starting point of PA promotion is sports. We chose to broaden our focus by including lifestyle-related activities (e.g. active transportation) that could be practiced daily. We also deliberately included non-athletic forms of PA (e.g. dancing, theatre), which may appeal to a broader part of the preschool children. Offering multiple entry points to PA may especially help to develop gender-specific approaches for PA promotion and may prove to be a more inclusive strategy, which may especially benefit immigrant children. Finally, our mixed methods evaluation strategy will enable insights into factors serving as barriers or facilitators to successful implementation of the intervention, thus strengthening the design of subsequent work in a relatively understudied but highly important population. Because a participatory approach has the potential to reveal unanticipated solutions as well as unexpected challenges that threaten intervention implementation and effectiveness, it is important that all participants including the research team use qualitative methods to enable learning.

Despite its strengths, we acknowledge several limitations of our study design. Our intervention does not target all levels of the system, in which preschoolers' behaviours develop. For example, the final menu of project ideas has not been developed in the teachers' environment and is not anchored within the curricular framework of the preschool teachers. Previous participatory research suggests that this might hamper the readiness of teachers to take ownership in the intervention change process [67]. Second, while stakeholders of the preschool communities participate in contents and structure, they are not included into the planning of the intervention. Therefore, our study cannot be characterized as community-based participatory research in a literal sense. However, a recent systematic review of community-based participatory research (CBPR) found only 4 of 60 CBPR studies demonstrating community participation across all research phases [68]. A further limitation of our participatory intervention is that the initial set of ideas was not refined and discussed with input from parents of children enrolled at the study preschools, but rather from parents obtained through a convenience sample of preschools prior to study inception. We will therefore explicitly check for differences in the discussions on the project ideas between the parents from the convenience-sampled versus the study preschools by means of qualitative data.

Although we were interested in using methods that promoted intervention sustainability, several factors may work against this. Our intervention, as currently proposed, will require some degree of parental time commitment at a level that might exceed parental resources. This may, in turn, threaten sustainability through fluctuations in parental time availability. In addition, changes in parental involvement may be expected as children graduate from kindergarten. To limit potential effects on the change process, we will seek ideas on how to minimize the knowledge and leadership drain, e.g. by encouraging effective documentation or by giving helpful hints to subsequent groups of parents in the last parent meeting during the formal intervention period. We anticipate that this sort of "sustainability planning" will be facilitated by placing implementation resources and project ideas on the study-dedicated website. Despite these efforts, greater reliance on teachers rather than parents may be required to successfully implement programmes that promote the adoption and routine practice of healthy behaviours.

As in any preventive intervention, the ultimate success hinges on building "capacity" - an intervention is only effective in the long run if it enables individuals or organizations to incorporate the goals of the intervention into their routine daily activities. The theory-based participatory approach used in this study can be conducive to capacity building by fostering a "pro PA" culture within the local preschool setting and providing resources to sustain new normative behaviours. Enriching children's environments with opportunities for PA may therefore become a normative expectation within the preschool community transmitted from the parents of one preschool class to the next. The effective implementation of participatory PA interventions in preschools might be one strategic element in lowering the public health burden of physical inactivity in younger children. Our study design, which employed a cluster randomized controlled design including a waiting-list and sought to avoid randomization imbalances by stratifying preschools according to average social class and to rural vs. non-rural natural setting, may serve as a role model for evaluating public health interventions in the preschool context.
